In Kano State where CHAI has historically assisted the Kano State Malaria Control Program (KSMCP) with SMC delivery, malaria is highly seasonal and spikes during the rainy season, typically during the two to four month period beginning in July/August of each year when SMC is recommended. The rainy season coincides with the “hunger season”, typically starting one month after the rains have begun. During these months children are extremely vulnerable to dying of causes that are completely preventable. One recommended treatment for malnutrition is Lipid-based Nutritional Supplements (LNS). Plumpy’DozTM is LNS designed for the treatment of moderate acute malnutrition and the prevention of undernutrition. Plumpy’DozTM is designed to sustain the growth of young children, improve their motor and cognitive development, and reduce the incidence of malnutrition—whether acute or chronic—during critical periods of food and nutrition insecurity. As they can be given without a medical prescription, LNS are often used in association with blanket feeding programs targeting young children who are not malnourished but who are at risk of malnutrition.

CHAI’s 2013 SMC pilot demonstrated that SMC coverage was optimized through door-to-door delivery of SP-AQ where nearly 90% of eligible children received at least one treatment course of SMC during the intervention period. As the 2014 SMC campaign will rely on the door-to-door delivery method, using the 2014 SMC campaign to deliver LNS could be one avenue for reaching children at-risk for both malaria and malnutrition at a critical time for both health concerns; however, to date this has never been done. Beyond reductions in malaria and malnutrition, packaging LNS with the SMC campaign may serve as an added incentive for parents/guardians to accept SMC preventative treatment, adhere to dosing guidelines, and incentivize caregivers to stay at home during regularly scheduled delivery periods resulting higher SMC coverage. CHAI, in collaboration with the KSMOH, will test SMC and LNS coverage, malaria, and malnutrition outcomes reached by packaging the delivery of LNS through the door-to-door SMC campaign.

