## 4 Intervention Design

### Study Site and Population

Table 4: Overview of the study population for each treatment type.

| Intervention Arm                                               | LGA    |
|----------------------------------------------------------------|--------|
| Arm 1: SMC (Children 3-59 months)                              | Madobi |
| Arm 2: SMC (Children 3-59 months) + LNS (Children 6-24 months) | Madobi |

This study has two intervention arms: SMC delivery and SMC + LNS delivery. Of note, SMC is specified by the WHO for children 3-59 months and Plumpy'doz' is specified by UNICEF and WFP for children 6-24 months, this study will treat children in intervention arms based on these recommendations (see Table 4: Intervention Arm). In the Local Government Area (LGA), Madobi, between 1 and 3 wards were selected for each intervention arm. An overview of the study population for each intervention area is presented in Table 4. The intervention areas were chosen to be as similar as possible in terms of pre-determined criteria that included malaria incidence reported at public health centers, wasting prevalence, malaria endemicity, socio-economic status, urbanicity, mobility and cultural identity of the population, density of health facilities, presence of a CMAM facility, and population demographic structures (dependency ratio, fertility rate and household size, infant mortality, and birth spacing).

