## 5 Monitoring and Evaluation Methods

Table 7 presents the data collection methods used for evaluation of the performance metrics previously outlined in Table 3, and the target population. Estimating intervention treatment coverage will be assessed through the midline cross-sectional household survey. The impact of interventions on nutrition health outcomes will be assessed through the three repeated cross-sectional household surveys. The impact of interventions on malaria health outcomes will be assessed through a case-control study using a malaria tracker where cases will be recruited from health facilities and control from the midline household survey. Cases will be recruited from facilities due to the challenge of identifying sufficient numbers of acute malaria episodes via monthly household surveys. Focus Group Discussions (FGDs) will be used to provide context to the results. CHAI will contract a private data collection firm to carry out the household surveys, case control study, collection of health facility records, and completion of FGDs. CHAI will carry out the data analysis and provide CIFF the full clean datasets from the firm upon request to validate findings.

Table 7: The data collection methods used for evaluation of the performance metrics previously outlined in Table 3, and the target population.

| Data Collection Method                                              | Timeline      | Inclusion Age*                | Location                     | Indicators                         |
|---------------------------------------------------------------------|---------------|-------------------------------|------------------------------|------------------------------------|
| Baseline Household Survey                                           | July 2014     | 6-24 months                   | Community                    | Malnutrition                       |
| Midline Household Survey
Nutrition Module
SMC Coverage Module | November 2014 | 6-28 months
(3-63 months)^ | Community                    | Malnutrition
Treatment Coverage |
| Endline Household Survey                                            | May 2015      | 12-34 months                  | Community                    | Malnutrition
Prevalence         |
| Malaria Case Tracker                                                | Continuous    | 6-24 months in July 2014      | Health Facility
Community | Malaria Incidence                  |

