### **Malaria Case Tracker**

In order to assess the relationship between the treatments and malaria health outcomes, a case-control study will be used. The study population includes any child between the ages 6-24 months in July 2014 residing in the interventions areas. The study will begin following the first round of administration, and will continue until adequate numbers of cases and controls have been recruited (with a maximum of two months following the final round of distribution even though the estimated sample size may not be reached). The outcome of interest is confirmed clinical malaria (including severe cases) with cases defined as any child from the study population with a positive malaria test by either a Rapid Diagnostic Test (RDT) or microscopy. Controls are defined as children whose caregivers report they meet the following two inclusion criteria: 1.) no previous malaria symptoms (no fever in the last 4-weeks) and 2.) no care was sought for fever or other malaria symptoms in any health facilities since beginning of July 2014) will be recruited as controls. The assessed exposure is whether the children received SMC, SMC and nutrition products, or neither.

Starting directly after the first administration period, cases and controls will be recruited from health facilities. Information from both cases and controls will be collected through a short (about 30 minutes), pre-tested, malaria-case tracker that covers demographics (age, gender, ward of residence), malaria symptoms and severity, and nutrition indicators, and intervention exposure status (whether the child received SMC or nutrition products). Health care workers will be trained on case eligibility criteria and will collect the data on the child from the parent/guardian. Health care workers will be given a job aid that will assist them in classifying severe versus uncomplicated malaria based on the child's symptoms using the Nigerian National Policy. Data from the tracker will be aggregated by a trained health care

worker on a weekly basis and collected by CHAI staff through routine visits. Small facilitations fees will be given to health facilities for participation.

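### The items listed for the malaria case tracker omit socio-economic status, net use and access to care, so the non-randomised H-3 odds ratios would carry residual confounding that later analysis cannot remove

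*Protocol*

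**What the plan says.** H-3, on the odds of diagnosed clinical malaria, is one of three primary hypotheses (Protocol, section 3, Table 2). Table 3 names the malaria case tracker as its data source. Under Malaria Case Tracker:

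- One form serves both groups: "Information from both cases and controls will be collected through a short (about 30 minutes), pre-tested, malaria-case tracker". It "covers demographics (age, gender, ward of residence), malaria symptoms and severity, and nutrition indicators, and intervention exposure status".
- Exposure is individual receipt: "The assessed exposure is whether the children received SMC, SMC and nutrition products, or neither".
- Cases are children with a positive RDT or microscopy result. Controls have had no fever in the last four weeks and no facility care for fever or malaria symptoms since the beginning of July 2014.

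Under Study Site and Population, arms are areas within one LGA: "between 1 and 3 wards were selected for each intervention arm". No randomisation is described. On comparability, "The intervention areas were chosen to be as similar as possible in terms of pre-determined criteria"; these include "malaria endemicity, socio-economic status, urbanicity, mobility and cultural identity of the population, density of health facilities".

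The source of controls is stated in two ways. The opening of section 5 says that "cases will be recruited from health facilities and control from the midline household survey". Malaria Case Tracker says that both cases and controls come from health facilities.

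**The concern.** Neither H-3 contrast is protected by randomisation, and each is exposed in its own way.

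- **Treated versus neither.** Receipt depends on the caregiver being at home and accepting. The Introduction itself treats this as behaviour that can be moved, expecting LNS to "incentivize caregivers to stay at home during regularly scheduled delivery periods resulting higher SMC coverage". Household traits behind acceptance may also bear on malaria risk and on attending a facility.
- **SMC + LNS versus SMC.** LNS is assigned by ward. Ward is on the form, but it determines the arm, so it cannot be used to adjust this contrast. The sample size is based on this contrast.

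The definitions of case and control add to the problem. A case must have reached a facility, and a control must not have sought facility care for fever or malaria symptoms. Access and care-seeking are thus tied to case status by design, yet no item on either is listed.

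The protocol names socio-economic status and facility density as features on which the areas should be alike, but lists no corresponding item for the individual child. An analysis plan can choose the model; it cannot supply answers never collected from cases.

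**Working it through.** **1. The plan's own figure.** Inputs from Malaria Case Tracker: exposure 60%, odds ratio 0.6, power 90%, alpha 5%.

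- Exposure in cases = 0.6 × 0.6 / (1 + 0.6 × (0.6 − 1)) = 0.36 / 0.76 = 0.4737.
- Comparing 0.4737 with 0.60, two-sided, 1:1, pooled variance, no continuity correction, gives 326 cases. This matches the protocol, and 4 × 326 = 1,304 controls.
- Power is 90.1% at 326:326 and 98.4% at 326:1,304.

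The figure is not in dispute. It is a crude comparison of two proportions with no allowance for covariates.

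**2. What the listed items allow.**

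| Item | Treated versus neither | SMC + LNS versus SMC |
|---|---|---|
| Age, sex | adjustable | adjustable |
| Ward | adjustable within an arm | not usable: ward determines arm |
| Nutrition indicators | with caution | with caution |
| Socio-economic status, net use, access to or use of care | not listed | not listed |

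Nutrition indicators need caution because they are measured after LNS has started and, in cases, during illness. They may be mediators or consequences.

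**3. Illustration of size.** The documents give no figures, so the inputs are assumptions: no treatment effect, and one unrecorded binary factor with odds ratio r for malaria, present in a proportion p1 of exposed and p0 of unexposed children.

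Crude odds ratio ≈ (p1·r + 1 − p1) / (p0·r + 1 − p0)

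- r = 0.5, 70% v 30%: 0.65 / 0.85 = 0.765
- r = 0.5, 60% v 40%: 0.70 / 0.80 = 0.875
- r = 0.7, 60% v 50%: 0.82 / 0.85 = 0.965
- r = 2, 60% v 40%: 1.60 / 1.40 = 1.143, so the bias can also run the other way

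Standard error of the log odds ratio with 326 cases and 1,304 controls:

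- 60% exposed: √(1/(326 × 0.24) + 1/(1,304 × 0.24)) = 0.126
- 90% exposed: √(1/(326 × 0.09) + 1/(1,304 × 0.09)) = 0.206

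The 60% is the protocol's planning value. The 90% reflects the Introduction's report that nearly 90% of eligible children received at least one course in the 2013 pilot, which may be nearer the mark for treated versus neither.

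The table shows each bias as a share of the planned log effect, ln 0.6 = −0.511, and the chance that a two-sided 5% test rejects when there is no effect.

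| Crude odds ratio | Share of planned log effect | Rejection, 60% exposed | Rejection, 90% exposed |
|---|---|---|---|
| 0.765 | 52% | 56% | 25% |
| 0.875 | 26% | 18% | 10% |
| 0.965 | 7% | 6% | 5% |

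**The case against.** **The list may be a summary.** The protocol describes the topics of a form of about 30 minutes, and the form itself is not shown. This stands as a caveat: if the missing items are already asked, the protocol need only say so.

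**More is recorded than age, sex and ward.** A reader might infer that the odds ratios cannot be adjusted at all. The documents do not support that: nutrition indicators are on the form, age and sex can be used in both contrasts, and ward can be used for treated versus neither within an arm. The gap concerns the unlisted factors only.

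**Other data exist.** A reader might also infer that nothing on file would allow a check. That goes too far. Phase 2 records the number of young children and the address for listed homes, registers hold an ID and location for each treated child, and the surveys collect household demographics in both arms, with coverage at midline. Arms, and treated and untreated children, can therefore be compared in part. No linkage of tracker cases to these sources is described, however, and demographics held for controls alone do not permit adjustment.

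**The areas were chosen to be alike.** This reduces average differences between arms, and it makes a 40-point gap in any factor hard to credit for SMC + LNS versus SMC. It does nothing about who accepts within an area.

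**Individual items cannot cure ward-level differences.** Correct: with one to three wards per arm, that part of the problem remains after any added items.

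**Net use asked of an ill child may reflect the illness.** Also correct. The item must refer to usual use before the illness.

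**Conclusion.** The point holds in limited form. As listed, the tracker omits socio-economic status, net use and access to or use of care, while exposure is not randomised and case status is tied to care-seeking. The H-3 odds ratios would keep residual confounding from these factors, and no later analysis could remove it because the items would not exist for cases.

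The size is unknown. The middle scenario (crude odds ratio 0.875; rejection about 18% at 60% exposed and about 10% at 90%) rests wholly on an assumed factor odds ratio and an assumed prevalence gap. The more extreme 0.765 is less plausible between arms. None of these scenarios reaches the design odds ratio of 0.6, so it should not be inferred that such confounding alone would explain a result of the planned size. It could shift an estimate noticeably in either direction.

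**What to change.** - Add a short set of items to the tracker, worded identically for cases and controls: usual net use (before the current illness in cases), caregiver education, a few household assets, travel time to the nearest facility, and household size. If the form already has them, list them in the protocol.
- Report the H-3 odds ratios adjusted for age, sex and these items, with the crude ones beside them.
- Reconcile the source of controls between the opening of section 5 and Malaria Case Tracker. If controls come from the midline survey, its questionnaire must carry the same items.
- State that SMC + LNS versus SMC stays open to ward-level confounding that individual items cannot remove.

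The cost is a slightly longer facility interview and a few more database fields. The change must be made before recruitment, since the answers cannot be obtained afterwards from the form.

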### **Phase 2: Intervention Administration**

Phase 2 will make use of the existing network of Community Drug Dispensers (CDDs) that work on other health campaigns in Kano. Community lists will be obtained for each ward from the Village head or the CDD LGA Focal person. Within each ward, CHAI study staff will visit each identified community and a household sampling frame will be obtained from each community headman. In the event that a Village head cannot produce an accurate listing or new communities have developed that are not present on the village head's list, the village headman and CDDs will be used to create a census of their community. CDDs alongside study staff will visit each household on the sampling frame and obtain accurate listings of homes with at least one child under-five residing within it in the treatment area. Supplementary data will also be collected from parents/guardians including data on the number of children 3-59 months of age residing in each home, child and parent's/guardian's names, and contact details (e.g. phone number of parent/guardian, address of home).

CHAI will train pre-existing CDDs on the proper administration of SP-AQ/*Plumpy doz'* in a 1-day training course. During each administration period, each CDD will be assigned to 100 households that they will cover over the course of one week. The CDDs will visit children and their parents/guardians in their homes four times on a monthly basis (July-October) and deliver the treatment. After each visit, CDDs will instruct parents/guardians that they will return four weeks later, on the *same day of the week* as the first SMC visit to deliver the next treatment.

All treatments provided will be recorded in two places: a treatment card that is left with the parent/guardian of the child and the CDDs administration register. Each child will be assigned a unique Identification number (ID) and the treatment card and the child's name in the CDDs administration register will be labeled with the unique ID. The treatment card will be filled out by the CDD at first contact, and given to the parent/guardian of each child. Information collected on the treatment card will include the child's name, birthday, dose of SP-AQ and amount of LNS provided, date of

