### **Treatment Registers**

Each CDD will be provided a treatment register at training and will be instructed on how to fill in the register. Every child that receives a dose of SP-AQ or SP-AQ + LNS will need to be entered into the treatment register before administration. As part of their involvement in this study, they will be requested to record the name, age, sex, and contact details of each child that they administer treatment to. If they do not feel able to complete the treatment register, they will not be able to participate in administration. It is expected to take less than 1 minute per patient to fill out the register. Study staff will collect the books after administration round 4. The purpose of the treatment registers is to provide on-going data on the number of treatments administered and to whom in each intervention area and assist with the development of the sampling frame for the control portion of the case-control study.

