### **Treatment Cards**

Every child 3-59 months in July 2014 reached by a CDD will be assigned an ID and their parent/guardian will be given a treatment card. Each time a child receives a treatment their parent/guardian will be asked to provide their treatment card and the CDD will record the dose and date of administration on the child's card as a record of the child's participation in the study. If the child is ineligible for treatment, the CDD will also record this on treatment card. The parent will be asked to keep the card in a safe place. The purpose of the treatment card is to provide a record of what treatment was provided, to which child, and the date of administration. It is both a record for the parent and will be also be referred to during the household survey.

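### For H-3, exposure comes from caregivers once the outcome is known, with no common record check, and the protocol contradicts itself on where controls come from, so the odds ratio can be biased either way

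*Protocol*

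**What the plan says.** **Case exposure.** The Malaria Case Tracker section states that health workers, once trained on who qualifies as a case, "will collect the data on the child from the parent/guardian". The data include intervention exposure, malaria symptoms and severity. A case needs a positive RDT or microscopy. The section names neither the treatment card nor the distributor register as a source for the exposure answer, and describes no masking.

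**Control source.** The opening of Section 5 says "cases will be recruited from health facilities and control from the midline household survey". The Malaria Case Tracker section says "cases and controls will be recruited from health facilities", and adds: "Information from both cases and controls will be collected through a short (about 30 minutes), pre-tested, malaria-case tracker". The Treatment Registers section brings in a third element: the registers are to "assist with the development of the sampling frame for the control portion of the case-control study".

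**Records.** Phase 2: Intervention Administration says "All treatments provided will be recorded in two places": a card left with the caregiver and the distributor's register. Both carry the child's unique ID, the SP-AQ dose, the LNS amount and the date. Of the card, the Treatment Cards section says: "It is both a record for the parent and will be also be referred to during the household survey". No section uses the card or the register to classify exposure in the case-control study.

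**The concern.** Treatment is open and exposure is obtained by interview. A facility worker who recruits on a positive test asks the parent of a sick child whether the preventive drug was given. Parent and worker would both normally know the outcome when the answer is recorded. A control is likewise interviewed as a child already known to be free of recent fever, because that is an entry condition.

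If controls come from the household survey, a second difference may be added: the card is consulted in that survey, but no card check is named for cases. A shared form does not by itself equalise the accuracy of the answer.

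When accuracy differs between cases and controls, the odds ratio moves away from its true value even if treatment does nothing, and recruiting more children does not correct it. Yet the study already makes a record at delivery, by people with no stated role in finding cases.

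**Working it through.** **Inputs from the protocol (Malaria Case Tracker):** coverage about 60%; detectable odds ratio 0.6, defined as SMC + LNS versus SMC alone; 326 cases; 1,304 controls (4 per case); power 90%; alpha 5%.

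**Assumed inputs:** the error rates. The protocol gives no sensitivity or specificity for caregiver report, so the values below only show a range.

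**Step 1: the plan's own figure.** With control exposure 0.60 and odds ratio 0.6, case exposure is 0.6 × 0.60 / (0.40 + 0.6 × 0.60) = 0.36 / 0.76 = 0.4737. The two-sided two-proportion formula at 1:1, without continuity correction, gives 326 cases. The stated number is reproduced, and this point does not affect it.

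**Step 2: error in cases only, treated versus neither, no true effect.** Observed exposure = p × Se + (1 − p) × (1 − Sp), with p = 0.60 in both groups. Controls are taken as correct, so their odds are 0.60 / 0.40 = 1.5.

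| Assumed error in cases | Observed case exposure | Observed odds ratio |
|---|---|---|
| 5% of treated reported untreated | 0.60 × 0.95 = 0.57 | (0.57/0.43)/1.5 = 0.88 |
| 10% | 0.60 × 0.90 = 0.54 | (0.54/0.46)/1.5 = 0.78 |
| 15% | 0.60 × 0.85 = 0.51 | (0.51/0.49)/1.5 = 0.69 |
| 5% of untreated reported treated | 0.60 + 0.40 × 0.05 = 0.62 | (0.62/0.38)/1.5 = 1.09 |
| 10% | 0.60 + 0.40 × 0.10 = 0.64 | (0.64/0.36)/1.5 = 1.19 |

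If all 326 cases and 1,304 controls entered this comparison, 5% or 10% under-report in cases alone would be declared significant about 17% or 50% of the time with no true effect (two-sided 5% test).

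**Step 3: equal error in both groups.** With Se = Sp = 0.90 throughout, observed exposure is 0.60 × 0.90 + 0.40 × 0.10 = 0.58 in cases and in controls, and the odds ratio is 1.00. At the null, the harm comes from a difference in accuracy between the groups.

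**Step 4: the powered contrast.** Let a and b be the numbers of cases truly given SMC + LNS and SMC alone, and let caregivers report a share s of treated children as treated. If s is the same in both arms, the reported odds are (s × a)/(s × b) = a/b, so the odds ratio is unchanged. If the shares differ, it is multiplied by their ratio: 0.95 against 0.90 gives 0.95/0.90 = 1.06, and the reverse gives 0.90/0.95 = 0.95. The Step 2 figures therefore do not transfer to this contrast.

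**The case against.** A reader might infer that controls are card-verified survey children, that cases are not, and that the odds ratio is therefore biased. The documents do not support this as settled fact:

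- The Malaria Case Tracker section also recruits both groups at facilities on the same tracker. On that statement the difference in source disappears, and what remains is reporting with the outcome known.
- The Treatment Cards section ties the card to the household survey in general. It does not mention the tracker or control exposure, and nothing bars a facility worker from reading the card.
- The contracted firm carries out the case-control study as well as the surveys, so the firm is no contrast between cases and controls.
- That the worker knows the test result is a close inference from the recruitment rule and the severity classification, but it is not stated.
- The error rates are assumed, and their direction is unknown.

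All of this stands, and it limits the point to a conditional one. The arms are also separate wards and the tracker records ward of residence, which gives some check on arm.

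Making register linkage the sole definition would bring its own error. The listed tracker demographics (age, gender, ward) contain no child ID. Registers list treated children, so a failed link could pass for no treatment. Entries are made before administration, so they do not prove ingestion.

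It can also be said that the ranking of exposure sources belongs in an analysis plan that is not at hand. That is fair for the ranking alone. It does not cover the contradiction on control source, or an identifier that must be collected in the field.

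**Conclusion.** The point holds in conditional form. The protocol gives two incompatible sources of controls and fixes no common exposure source for cases and controls. If the household-survey statement governs, the accuracy of exposure data can differ by case status. Under either statement, exposure is reported with the outcome known. The odds ratio can be biased, in a direction that the documents do not determine.

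For treated versus neither, the illustrated range at no true effect is 0.69 to 1.19. It rests on 60% exposure, error-free controls and assumed error of 5–15% (under-report) or 5–10% (over-report) in cases only.

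A reader might set this range against the design odds ratio of 0.6 and conclude that much of the planned effect could be artefact. That comparison is not valid: 0.6 refers to SMC + LNS versus SMC alone, where under-report equal across arms cancels. The concern reaches that contrast only if the error differs by arm.

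This should be changed. The means are already in the study, and the step cannot safely be left until later: the tracker's listed contents carry no linking ID, and Data Management and Confidentiality has identifiers destroyed when analysis is complete.

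**What to change.** 1. Reconcile the opening of Section 5 with the Malaria Case Tracker section so that both name the same source of controls, and state how the registers serve the control sampling frame.
2. In the Malaria Case Tracker section, add the child's unique ID to the tracker, or name, village and birth date where the ID is not available.
3. Classify exposure for cases and controls by the same rule: treatment card seen, then confirmed or replaced by the distributor's register, linked by ID by staff masked to case status.
4. Treat a child with no card and no link as exposure unknown, not as neither. Use caregiver report only as a labelled fallback and in a sensitivity analysis. Report the unknown and fallback numbers by case status.

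**Cost.** A few added tracker fields and linkage work on registers already collected; no new visits. Some children will not link. Children whom the distributors never reached have no card, so part of the true neither group will still rest on caregiver report. The records document delivery, not ingestion.
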